# Effect of virtual reality exposure therapy on social participation in people with a psychotic disorder (VRETp): study protocol for a randomized controlled trial

**DOI:** 10.1186/s13063-015-1140-0

**Published:** 2016-01-13

**Keywords:** Psychosis, Schizophrenia, Paranoia, Interaction anxiety, Virtual Reality, Exposure, Social participation, Therapy

## Abstract

**Background:**

Many patients with a psychotic disorder participate poorly in society. When psychotic disorders are in partial remission, feelings of paranoia, delusions of reference, social anxiety and self-stigmatization often remain at diminished severity and may lead to avoidance of places and people. Virtual reality exposure therapy (VRET) is an evidence-based treatment for several anxiety disorders. For patients with a psychotic disorder, the VRETp was developed to help them experience exposure to feared social situations. The present study aims to investigate the effects of VRETp on social participation in real life among patients with a psychotic disorder.

**Methods/design:**

The study is a single-blind randomized controlled trial with two conditions: the active condition, in which participants receive the virtual reality treatment together with treatment as usual (TAU), and the waiting list condition, in which participants receive TAU only. The two groups are compared at baseline, at 3 months posttreatment and at 6 months follow-up. All participants on the waiting list are also offered the virtual reality treatment after the follow-up measurements are completed. The primary outcome is social participation. Secondary outcomes are quality of life, interaction anxiety, depression and social functioning in general. Moderator and mediator analyses are conducted with stigma, cognitive schemata, cognitive biases, medication adherence, simulator sickness and presence in virtual reality. If effective, a cost-effectiveness analysis will be conducted.

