### Cost-effectiveness

The Trimbos/iMTA questionnaire for Costs associated with Psychiatric illness (the TiC-P) is designed for self-report by patients with a mental disorder. The questionnaire focuses on establishing direct medical costs and productivity costs during paid or unpaid work. The psychometric properties are reported to be adequate [40].

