### Power and sample size calculation

In this RCT, the effect of VRETp on social participation is investigated by comparing this treatment with a waiting list condition. Social participation is assessed with the PsyMate experience sampling method (ESM; see “Measurements”). Self-assessments are rated on a 7-point Likert scale. Main outcome items are social environment and company, perceived social threat in company, event stress, and momentary paranoia. Estimated mean scores and standard deviations (SD) are not readily available because there are no previous VRETp studies with psychotic patients.

Using an estimated (moderate) effect size of 0.5 with a power of 0.8, an alpha of 0.05 and a two-sided independent *t* test, yields *n* = 64 in each group. Therefore, at least 64 participants need to be included in each arm (total *n* = 128 patients). As attrition is estimated at about 20 %, 80 participants need to be included in each condition (total *n* = 160 patients).

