#### Data analysis

Multilevel linear mixed modeling is used to analyze the data according to the intention-to-treat principle. Completer analysis is conducted with analysis of variance (ANCOVA). Moderator and mediator analysis is conducted to assess the effects of moderators and mediators. Cost-effectiveness is conducted with social participation as the outcome.

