## Discussion

The main goal of the study is to investigate the effect of VRETp on improving social participation in patients with psychosis in real life. We hypothesize that VRETp will increase social participation objectively (time spent in company) and subjectively (experience less anxiety and paranoia during in social situations). Comparison between VRETp treatment and a waiting list condition will provide information about the effectiveness of VR exposure therapy for this population. This should make an important contribution to treatment options for people suffering from psychosis and social isolation. Improving social participation is of great personal value to patients with psychosis who suffer from the consequences of avoiding social situations in daily life.

In addition to social participation, the effect of VRETp on psychological, emotional and social well-being, especially paranoia and interaction anxiety, is explored. Studying these variables may help disentangle the complex phenomena related to social participation in patients with psychosis.

Another aspect of the study is cost-effectiveness. If social participation improves it is expected that patients will become more independent, consume less care and, thereby, diminish costs related to extended health care.

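### The Abstract makes the cost-effectiveness analysis depend on an undefined finding of effectiveness, a condition absent from the objectives and the analysis section

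*Protocol article*

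**What the plan says.** The condition stands in one place, the Methods/design paragraph of the Abstract: "If effective, a cost-effectiveness analysis will be conducted".

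The rest of the article carries no such condition:

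- **Secondary objectives:** the cost-effectiveness of VRETp is listed alongside acceptability, the clinical secondary outcomes, and moderation and mediation.
- **Data analysis:** "Cost-effectiveness is conducted with social participation as the outcome".
- **Discussion:** "Another aspect of the study is cost-effectiveness".
- **Table 1:** the TiC-P is scheduled at T0, T3 and T6. Of this instrument the Cost-effectiveness section says "The questionnaire focuses on establishing direct medical costs and productivity costs during paid or unpaid work".

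No section says which measure, at which time point and by what criterion, would make VRETp effective for this purpose. The Power and sample size section names four main outcome items: social environment and company, perceived social threat in company, event stress, and momentary paranoia. The Design section compares the groups at post-treatment and at follow-up.

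**The concern.** Two things are at stake.

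**Result-dependent reporting.** If the Abstract governs, a trial that is not judged effective drops a stated secondary objective, even though the cost data have been collected. Because the trigger is undefined, the decision could also be taken once the results are known, with a choice among four outcome items and two time points.

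**The wrong kind of rule.** An economic evaluation weighs the difference in cost against the difference in effect, with the uncertainty of both. An imprecise effect combined with clear savings, or with clear added cost, can still inform a decision on adoption. The Data analysis section also makes social participation, the primary outcome, the effect measure of the economic analysis. The natural reading is that the same estimate would first decide whether the analysis is run and then serve as its effect. Across repeated trials, the effects used in reported analyses would then be a selected, upwardly biased set.

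**Working it through.** **1. The places side by side.** The Abstract has a condition. The Secondary objectives, Data analysis and Discussion have none, and the data collection in Table 1 does not depend on one. The article therefore does not settle whether the objective is reported after a disappointing primary result.

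**2. The plan's own sample size.** The inputs come from the Power and sample size section: "Using an estimated (moderate) effect size of 0.5", "with a power of 0.8", and "an alpha of 0.05 and a two-sided independent" t test. No SD is given ("Estimated mean scores and standard deviations (SD) are not readily available because there are no previous VRETp studies with psychotic patients"), so I work on the standardised scale with SD = 1.

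- The exact two-sided t test needs 63.77 per arm, so 64. Power at 64 is 0.801.
- Allowing for 20% attrition: 64 / 0.8 = 80 per arm.

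Both stated figures reproduce and are not in dispute.

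**3. Illustration under one assumed trigger.** Assume that effective means two-sided p<0.05 in favour of VRETp on one standardised outcome, with 64 analysed per arm.

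- SE = √(2/64) = 0.177.
- The critical value of t on 126 degrees of freedom is c = 1.979, so an estimate counts as significant above 1.979 × 0.177 = 0.35.
- With a = c − d/SE, the chance of passing is P = 1 − Φ(a), and the mean estimate given a pass is d + SE × φ(a)/P.

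At d = 0.5: a = 1.979 − 2.828 = −0.849, P = 0.802 and φ(a) = 0.278. The mean estimate is 0.5 + 0.177 × 0.278/0.802 = 0.561, and 0.561/0.5 = 1.12.

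| True d | Analysis skipped | Mean estimate when run | Ratio to truth |
|---|---|---|---|
| 0.5 | 20% | 0.56 | 1.12 |
| 0.4 | 39% | 0.51 | 1.28 |
| 0.3 | 61% | 0.47 | 1.58 |

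Using 1.96 in place of 1.979 gives 19%, 38% and 60% skipped, with ratios of 1.12, 1.27 and 1.57. If the analysis is always run, the mean estimate equals the true d.

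**4. How far this depends on the trigger.** I simulated four equally affected outcomes, each with d = 0.5 and 64 per arm. The pairwise correlations of 0.3 to 0.7 are my assumption, since the article gives none.

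| Trigger at d = 0.5 | Analysis skipped | Mean inflation of a given outcome |
|---|---|---|
| One named outcome | 20% | 12% |
| Any one of four | 1% to 6% | 1% to 4% |
| All four | 37% to 49% | 17% to 18% |

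**The case against.** **The article does not strictly contradict itself.** A reader might infer that the Abstract overturns an express promise of an unconditional analysis. The documents do not go that far. The Secondary objectives name a topic and the Data analysis section names an outcome measure; neither says the analysis runs whatever the result. Silence is compatible with a condition stated elsewhere, and the Discussion itself reasons conditionally, expecting lower costs if participation improves. This stands. The defect is a condition in one place that is missing from the others, not two opposed statements.

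**A significance gate is an inference.** The Abstract attaches no test or threshold to the word effective, and a definition may sit in a fuller document that is not shown. This also stands, so the figures above are illustrations and not properties of the plan. They further assume a t test with 64 per arm, whereas the plan recruits 80 per arm to allow for attrition and analyses with multilevel mixed models.

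**Removing the condition changes no estimate in a trial that passes.** A reader might infer that the condition distorts the analysis itself. It does not: a trial judged effective would report the same estimate and the same cost per unit gained with or without it. The inflation is an average over repeated trials, and it applies to any result picked out for being significant. This stands too. What the fix removes is non-reporting when the result is unfavourable.

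None of this rescues the condition. Under any trigger, whether a stated objective is reported would depend on the outcome, and the article gives no reason why it should.

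**Conclusion.** The point holds as a matter of result-dependent reporting on an undefined trigger. The Abstract's condition, if followed, would suppress a stated secondary objective in some trials although the cost data exist.

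On the illustrative single-outcome rule, that happens about one time in five at the design effect of 0.5 and about two times in five at d = 0.4. The mean inflation of the effects that do get reported is modest at d = 0.5 (about 12%) and larger if the true effect is smaller. These numbers rest on an assumed trigger of p<0.05, 64 analysed per arm and a standardised scale. Under other plausible triggers at d = 0.5, the share of trials skipped runs from about 1% to 49%.

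Randomisation, sample size, data collection and the primary analysis are not affected. The change is worth making because it is simple and closes a route to selective reporting.

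**What to change.** Delete the opening condition from the Abstract sentence. State there and in the Data analysis section that the cost-effectiveness analysis is done and reported in all randomised patients regardless of the primary result, with social participation as the effect measure as already planned, and with the joint uncertainty of costs and effects. How that uncertainty is displayed can be left to the analysis plan.

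The cost is a sentence or so of text and a small amount of extra analysis. The TiC-P is already scheduled at T0, T3 and T6, so sample size, visits and data collection do not change.

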**Discussion:**

Results from the posttreatment measurement can be considered strong empirical indicators of the effectiveness of VRETp. The 6-month follow-up data may provide reliable documentation of the long-term effects of the treatment on the outcome variables. Data from pre-treatment and mid-treatment can be used to reveal possible pathways of change.

**Trial registration:**

Current Controlled Trials: ISRCTN12929657. Date of registration: 8 September 2015

## Background

A large number of patients with a psychotic disorder participate poorly in society, even if their psychotic symptoms have been treated successfully. Unemployment is high at 80–85 % [1] and about 75 % do not have a relationship with a partner [2]. A study comparing the social network of young people with early psychosis and matched controls showed that the psychosis group had smaller networks, fewer friends, fewer people to turn to in a crisis, and a greater likelihood of service providers as members [3]. Social network size is also associated with the likelihood of in-patient treatment and with the number of services used by psychotic patients [4]. Social isolation hinders patients in multiple areas of functioning, such as developing and maintaining a social network, the ability to function in work-related environments, and even in performing daily tasks needed for independent living (e.g., shopping for groceries). When psychotic disorders are in partial remission, the remaining feelings of paranoia and delusions of reference often cause patients to avoid places and people. Moreover, this conditioned avoidance does not improve with antipsychotic medication [5].

**Table 1 Tab1:** Measurement objectives

Outcome	Measurement	T0	T1	T2	T3	T6
	Interview (i) Self-report (s)	Baseline	Session 4	Session 8	Posttreatment	Follow-up
Social participation	Experience Sampling Method (s)	x			x	x
Paranoia	GPTS (s)	x	x	x	x	x
Interaction anxiety	SIAS (s)	x	x	x	x	x
Depression	BDI-II (s)	x			x	x
Stigma	ISMI (s)	x			x	x
Schemas	BCSS (s)	x			x	x
Safety behavior	SBQ (i)	x			x	x
Cognitive biases	DACOBS (s)	x			x	x
Social functioning	SOFAS (i)	x			x	x
Quality of life	MANSA (i)	x			x	x
Cost-effectiveness	TIC-P (i)	x			x	x
Cyber sickness	SSQ (s)		x	x		
Presence	IPQ (s)		x	x		
Medication adherence	BARS (i)	x	x	x	x	x

*GPTS* Green et al. Paranoid Thought Scales, *SIAS* Social Interaction Anxiety Scale, *BDI-II* Beck Depression Inventory, *ISMI* Internalized Stigma of Mental Illness, *BCSS* Brief Core Schema Scales, *SBQ* Safety Behavior Questionnaire – persecutory delusions, *DACOBS* Davos Assessment of Cognitive Biases Scale, *SOFAS* Social and Occupational Functioning Assessment Scale, *MANSA* Manchester Short Assessment of quality of life, *TiC-P* Trimbos/iMTA questionnaire for Costs associated with Psychiatric illness, *SSQ* Simulator Sickness Questionnaire, *IPQ* Igroup Presence Questionnaire, *BARS* Brief Adherence Rating Scale

### Exposure

The evidence-based psychological treatment for experiencing fear and paranoia in social situations is cognitive behavioral therapy (CBT) with exposure in vivo, such as the therapist taking a patient shopping or exposing the patient to public transportation. This form of treatment in vivo has several limitations. First, the social world in which in vivo exposure takes place cannot be experimentally manipulated. Second, exposure therapy in vivo is costly and not readily available in most mental healthcare institutes. Third, therapy sessions are used to prepare exposure exercises, which the patient is expected to perform between sessions; however, even with careful tailoring to the patients’ capabilities, it is often difficult for patients to do these exercises as planned. Fourth, not all patients tolerate exposure in vivo.

### Anxiety disorders and VRET

Virtual reality exposure therapy (VRET) is an evidence-based treatment for several anxiety disorders [6]. It has the potential to be an affordable and accessible form of treatment to enhance social participation and wellbeing for patients suffering from a psychotic disorder and social withdrawal. In virtual worlds fear is experienced similar to the in vivo experience. It is the experience of being there (known as ‘presence’), which the three-dimensional virtual reality (VR) environment creates, together with a narrative about the environment, that enables people to feel and behave as they would in real life. This principle makes it possible to overcome fear and practice new behavior in a virtual environment [7]. An advantage of VR is that people find it easier to start exposure, since they know there is no real threat to their safety [8]. In students suffering from fear of spiders, 81–89 % chose VR exposure over in vivo exposure [9]. A study comparing VR exposure vs. in vivo exposure in specific phobias showed that 76 % of the patients chose VR exposure over in vivo exposure [10]. The refusal rate for in vivo exposure (27 %) was higher than that for the VRET (3 %). In total, 90.4 % of the patients that preferred VR exposure said they did so because they were too afraid to confront the real situation or to object. These results suggest that the availability of VR exposure may increase the number of patients who are willing to engage in exposure-based therapy.

### VRET in psychosis

In a VRET treatment protocol, patients are gradually exposed to controlled social environments that induce fear and in which individually tailored exposure exercises can be designed. The ability to provide fear-inducing VR social environments is partially dependent on the availability of anxiety-provoking stimuli in the software of the virtual worlds. The present study will assess whether the currently used anxiety-provoking stimuli sufficiently match the stimuli asked for by patients during treatment.

An experimental virtual world was developed. The ecological validity of the VR environment has been demonstrated. For patients suffering from psychosis a significant correlation was found between paranoia and social interaction anxiety in real life and paranoid thoughts about the avatars in the VR world [11]. A higher degree of paranoia was found when more avatars were present, when avatars had hostile facial expressions, and when more of the avatars had a different ethnicity [12].

Preliminary findings using VRET with psychosis show that patients experiencing paranoia are willing to participate in VR environments, that they report paranoid thoughts about the virtual people (avatars), but at the same time are willing to confront the fearful situation [11, 13]. Social virtual environments have the potential to enhance CBT by helping patients recovering from psychosis to understand the role of avoidance and safety behaviors in the maintenance of interaction anxiety and paranoia. Additionally, it can enhance their confidence to carry out real-life behavioral experiments [14].

### Side effects and safety

A phenomenon called simulator sickness (also known as cyber sickness) can occur when using VR applications. Symptoms are similar to those of motion-induced sickness, but tend to be less severe and have a lower incidence [15]. It is suggested that simulator sickness sensations can be at least partially explained by an overlap with anxiety symptoms [16]. A pilot study on virtual reality and psychosis showed low symptoms of simulator sickness, and no significant increase between pre- and post-measurement [11]. Since simulator sickness is known to increase with the duration of exposure [15], measurement of these symptoms will be included in the study protocol.

No adverse effects were found in studies using VR to expose psychotic patients to virtual social environments. A study with 20 psychotic patients diagnosed with first-episode psychosis experiencing at least moderate paranoia found that VR did not lead to more anxiety or physical complaints directly after the experiments; follow-up 1 week later showed that no patients reported an increase in intrusive negative thoughts, unpleasant emotions or behavioral changes as a consequence of the VR experience [16]. Similar results were found in a study of 21 patients with at-risk mental state for psychosis [8]. Our own pilot study confirmed that patients did not become more psychotic as a result of exposure to our virtual social environment [11].

### Objectives

As this is a new form of treatment for social withdrawal in psychosis, the first step is to demonstrate the effect of VRET compared to a waiting list condition on social participation in real life. Objective social participation is defined as the time spent in social situations with other people and the time spent interacting with other people in everyday life. Subjective social participation is how patients experience these social situations; this experience is expressed as momentary paranoia, perceived social threat and event stress, as experienced in situations with other people.

We hypothesize that, after applying the intervention for patients with paranoia (VRETp), they will show improved social participation.

### Primary objective

To determine the effectiveness of VRETp in patients with psychosis, defined as improved social participation.

Hypothesis 1: The amount of time spent with other people will increase, as measured 60 times a week in real life.

Hypothesis 2: Momentary paranoia, perceived social threat and event stress as experienced in social situations will decline, as measured 60 times a week in real life.

### Secondary objectives

Secondary objectives are to investigate:the acceptability of VRETp for patients and therapiststhe effects on interaction anxiety, depression, quality of life and social functioning in generalthe moderating and mediating effects of stigma, schemata about the self and others, cognitive biases, medication adherence, simulator sickness and experienced presence in the VR environmentthe cost-effectiveness of VRETp

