### Presence

The Igroup Presence Questionnaire (IPQ) consists of 14 items assessing sense of presence in virtual environments. Responses are made on a 7-point Likert scale. The IPQ has demonstrated good psychometric properties [39].

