### Procedure

Patients with a chart diagnosis of schizophrenia, schizophreniform disorder, schizoaffective disorder, delusional disorder or psychotic disorder not otherwise specified (NOS), will be informed about the study by their treating specialist and asked to participate. Each patient is asked for written permission to be contacted by the researchers if eligible for VRETp. If eligible, the treating specialist discusses participation of the patient in the study with the remainder of the team and gives permission to the researchers to contact the patient. When permission is given, additional information is provided and patients have 2 weeks to consider whether they really wish to participate. The VRETp treatment is additional to current treatment and declining to participate has no negative consequences at all for patients. For each of the participating organizations an independent specialist is available for patients to contact. Contact information of this specialist is available in the information letter given to the patients of the participating organizations.

Informed consent from all participants is obtained before assessment by the researcher. The MINI-Plus interview is used to diagnose psychotic disorders. Patients who are willing to participate are screened for avoidance behavior (SBQ) and for paranoia using the GPTS (cutoff >40) of Green et al. Baseline measurements are obtained. Randomization is used to allocate a patient to either the VRETP or to the waiting list condition. Patients allocated to the VRETp group start their treatment, which consists of a maximum of 16 sessions with a maximum duration of 60 minutes each.

At baseline (T0) the research assistant assesses the baseline measurement of all primary and secondary variables. At 2 weeks (T1) and 4 weeks (T2) into treatment, respectively, participants in the treatment condition are assessed for their scores on paranoia, interaction anxiety, cyber sickness, presence in the virtual world and medication adherence, using self-report questionnaires handed out by the therapist, or interview questions (medication adherence).

At the end of treatment (T3) and at follow-up (T6), the research assistant assesses the primary and secondary measures.

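### Simulator sickness and VR presence are listed as moderators and mediators but are measured only in the VRETp arm after treatment starts, so neither role can be tested for the VRETp-versus-waiting-list effect

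*Protocol article*

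**What the plan says.** The Abstract (Methods/design) states: "Moderator and mediator analyses are conducted with stigma, cognitive schemata, cognitive biases, medication adherence, simulator sickness and presence in virtual reality". The Secondary objectives repeat the list, ending with "medication adherence, simulator sickness and experienced presence in the VR" environment. In the Methods, the SSQ and IPQ are both described under the heading for moderators and mediators. The Data analysis section adds only: "Moderator and mediator analysis is conducted to assess the effects of moderators and mediators". It does not separate these two variables from the other four.

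The schedule is explicit. Table 1 marks SSQ and IPQ at T1 (session 4) and T2 (session 8) and nowhere else. The Procedure section says that at those visits "participants in the treatment condition are assessed for their scores on paranoia, interaction anxiety, cyber sickness, presence in the virtual world and medication adherence". Under Design, the waiting-list arm is offered VR only once follow-up measurements are finished, at 6 months. Under Presence, the IPQ "consists of 14 items assessing sense of presence in virtual environments", so it has no meaning for someone who has not been in one.

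**The concern.** The Objectives section frames the effect of interest as VRET against a waiting list. A moderator of that effect is a characteristic fixed before randomisation, across whose levels the difference between arms varies. A mediator is a post-randomisation variable that treatment changes and that in turn changes the outcome, so it must have a value under both conditions. SSQ and IPQ meet neither description: they come after randomisation and do not exist in the control arm during the comparison.

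At stake is how the result would be read. A correlation inside the VRETp arm between presence and later social participation could be presented as the mechanism, or as a modifier, of a randomised effect. If control values were filled in with a constant, software would return an indirect effect whose size and sign depend on that constant.

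**Working it through.** **Inputs.** A = 1 for VRETp and 0 for waiting list. M = SSQ or IPQ score, observed only where A = 1 (Table 1, Procedure, Design). Y = outcome. From the Power section: effect size 0.5, power 0.8, two-sided alpha 0.05, 64 per arm, 20% attrition.

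**The plan's own figure.** The exact two-sided t test gives 63.77, hence 64 per arm (power 0.801). Allowing for attrition, 64 / 0.8 = 80 per arm, 160 in total. The stated sample size reproduces and this point does not affect it.

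**Moderation.** Model: Y = β0 + β1·A + β2·M + β3·A·M.
- On rows with M observed, A is always 1. The intercept and A columns coincide, and so do M and A·M. The rank is 2 of 4.
- With M set to 0 in controls, M and A·M are the same column. The rank is 3 of 4.
- With any other constant c in controls, M = A·M + c·(1 − A), again an exact linear dependence.

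β3, the moderation effect, is not identified in any of these cases.

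**Mediation.** Models: M = a0 + a·A and Y = b0 + c′·A + b·M.
- On observed rows the first has rank 1 of 2 and the second rank 2 of 3. Neither a nor c′ can be estimated.
- Filling controls with a constant c makes the models run, but the indirect effect becomes b × (mean M in VRETp − c), which depends on c.

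In one constructed data set (not trial data) with b = 0.03, mean M in VRETp of 29.27 and a total effect of 0.48:

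| Control fill-in c | Indirect = 0.03 × (29.27 − c) | Direct | Total |
|---|---|---|---|
| 0 | 0.88 | −0.40 | 0.48 |
| 10 | 0.58 | −0.10 | 0.48 |
| 50 | −0.62 | 1.10 | 0.48 |

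The total is fixed, while the split between direct and indirect is set by the fill-in value. More patients would not change this.

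**What remains estimable.** A correlation within the VRETp arm can be estimated. The smallest detectable value with 80% power and two-sided alpha 0.05 (Fisher z) is tanh[(1.960 + 0.842) / √(n − 3)]:
- n = 64: tanh(2.802 / 7.810) = 0.34
- n = 80: tanh(2.802 / 8.775) = 0.31

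**The other four variables.** Table 1 has ISMI, BCSS, DACOBS and BARS at T0, T3 and T6, and only T1 and T2 are confined to the treatment condition. Their T0 values can serve as moderators and their later values in both arms as candidate mediators.

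**The case against.** The strongest reply is that the protocol writes down no interaction term and no mediation path. The model is commonly left to the SAP, which is not shown, and the six variables are listed jointly without saying that each is tested in both roles. The Abstract's Discussion also says that pre-treatment and mid-treatment data may show how change comes about. Since mid-treatment data exist only in the treated arm, some process use within VRETp was plausibly foreseen. This has weight: it suggests loose labelling rather than an unworkable programme. It does not remove the conflict, because that sentence names neither variable, while the objective and the Abstract do name them as moderators and mediators. No SAP can supply control values that the schedule never collects.

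Two stronger readings are tempting and are not supported.
- A reader might infer that SSQ and IPQ cannot be analysed at all. Non-identification applies to the between-arm effect only. Associations within the VRETp arm are estimable, and methods such as principal stratification exist, though they rest on untestable assumptions and are not planned.
- A reader might infer that the missing T0 SSQ is part of the error and makes the sickness data uninterpretable, because the Side effects and safety section says that "simulator sickness sensations can be at least partially explained by an overlap with anxiety symptoms". That section presents this as a suggestion and a partial explanation. It gives a different reason for measuring sickness, its rise with duration of exposure. No change-from-baseline SSQ analysis is planned, and SIAS and GPTS at T0, T1 and T2 allow adjustment for anxiety and paranoia.

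**Conclusion.** The concern holds in a limited form. For two of the six listed variables, the stated moderator and mediator analyses of the VRETp-versus-waiting-list effect cannot be delivered by the stated schedule, whatever the sample size. This follows from Table 1, Procedure and Design alone. It assumes that moderation and mediation carry their usual meaning with respect to the comparison between arms; nothing in the protocol gives them another.

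The consequence is confined to part of one of four secondary objectives. The primary hypotheses, randomisation, sample size and intention-to-treat model are untouched, and the four remaining variables can be analysed as planned. It should be corrected before analysis, but it does not threaten the trial's main conclusion.

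**What to change.** - Remove SSQ and IPQ from the moderator/mediator list in the Abstract, the Secondary objectives and the Methods heading.
- Describe them as exploratory process measures within the VRETp arm: association of T1/T2 scores with the T3 outcome, adjusted for T0 outcome and T0 SIAS and GPTS, labelled non-randomised.
- Use T0 values of ISMI, BCSS, DACOBS and BARS as moderators, and keep their post-baseline values measured in both arms (T3, T6) as candidate mediators. The T1/T2 BARS values exist only in the VRETp arm and should not be used for mediation.

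The cost is rewording, with no change to sample size or visits. The downside is that the SSQ and IPQ analyses draw on one arm only, with the limited sensitivity shown above, and cannot support a causal claim about the randomised effect.

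Optionally, give the self-report SSQ at T0 to patients still to be enrolled. Because the trial is ongoing, this would cover later enrollees only, in unknown number. It would allow change from baseline but, without concurrent control values, not full attribution to VR.
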